#### 4.4 Sample size calculation

Based on our FMT pilot study  and the study of *A. soehngenii* in MetSy (average GLP1 increase: 42%), taking into account the additional potential benefits of the synbiotic treatment approach, we performed a power analysis to calculate the number of participants necessary to detect a 25% reduction in our primary outcome parameter, reversal of steatosis and necro-inflammation following donor FMT combined with the synbiotic treatment. For a desired alpha of 0.05 and a desired power of 0.8, a sample size of 24 participants/arm will be required, ergo 48 total.

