## 10. STATISTICAL ANALYSIS

Statistical analyses will be performed by SPSS statistical analysis software and R-studio.

Normality of the data will be assessed by a Kolmogorov–Smirnov test. Data transformation will be done if the data is not normally distributed. The primary analyses of studied primary parameters will be performed between the baseline and endpoint intervention by analysis of a two-tailed one-sample t-test, or chi-square test. If the data is not normally distributed and data transformation is not possible, the Mann-Whitney test will be used. Further associations will be assessed with Pearson rank correlation test / Pearson chi-square test.

Paired categorical data will be analyzed with McNemars test. Paired continuous data will be analyzed using a paired T-test when normally distributed, and a Wilcoxon signed-rank test when not normally distributed.

Using R, we will use statistical packages that employ machine-learning algorithms to reveal which metabolites and microbiota best predict favourable response. An Elastic Net machine learning classification algorithm in combination with a stability selection procedure will be used to identify biological features that change differently between the two treatment groups. Also using R, a deep-learned algorithm scoring whole slide images of liver biopsies will be applied and analyzed.

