### **11.3 Benefits and risks assessment, group relatedness**

#### *Benefits*

NAFLD and NASH have an enormous and increasing prevalence: 20-30% of the global population has NAFLD to some extent. NAFLD-related livercirrosis is a growing indication for liver transplantation and the incidence of NASH-related hepatocellular carcinoma is

increasing. The disease progresses slowly and NASH-liver fibrosis is strongly associated with atherosclerotic cardiovascular disease and liver-related and overall mortality. Nevertheless, there is no registered or proven treatment for progressed stages of NAFLD-NASH.

As previously stated, extensive prior research associates the gut microbiome with NAFLD-NASH. Regardless, these studies did not entail a treatment targeting the microbiome to reduce NAFLD-NASH, which would be a big step in the field. Based on available literature on treatment with synbiotics in NAFLD/NASH-patients and our pilot study on FMT in NAFLD/NASH-patients, this trial with adequate sample size endeavours to study if modification of the gut microbiome can attenuate NASH and liver fibrosis.

The benefits the study entails will be discussed in three sections. First, we expect a short term benefit for participants. Our underpowered study in which we administered FMT in NAFLD, showed a trend to reduction of necro-inflammation (i.e. inflammation and ballooning) in histopathological examination. Inflammation and ballooning are the most important predictors of progression of NAFLD-NASH, and subsequent secondary complications. The current study will use LFMT capsules instead of fresh FMT per nasoduodenal tube. This will strongly reduce the burden on participants and will more closely resemble a realistic treatment for NASH. Moreover, recent studies show that LFMT capsules have the same efficacy and show a similar shift of the microbiota composition towards a donor profile, indicating similar engraftment. Half of the individuals will receive the LFMT capsules, and we expect that this already will attenuate NASH. All participants will, in addition, be treated with a complementary synbiotic combination. Multiple small clinical trials already showed a beneficial effect of synbiotics on NAFLD-NASH, without entailing serious side effects. Therefore, we expect a beneficial effect of the synbiotics in both study arms.

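### Section 4.4 does not support 80% power with 24 per arm for a 25-point between-arm difference in the section 8.1.2 composite, except at extreme response rates, and it omits the inputs behind the figure

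*Protocol*

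**What the plan says.** Protocol section 4.4 states its aim: "we performed a power analysis to calculate the number of participants necessary to detect a 25% reduction in our primary outcome parameter". It sets the effect to be found as follows: "detect a 25% reduction in our primary outcome parameter, reversal of steatosis and necro-inflammation". The error rates are "For a desired alpha of 0.05 and a desired power of 0.8", and the conclusion is "a sample size of 24 participants/arm will be required, ergo 48 total". The section refers to the FMT pilot, to a GLP1 rise seen with *A. soehngenii*, and to extra benefit expected from the synbiotic. It states no control response rate, standard deviation, sidedness or test, and does not say whether the 25% is absolute or relative.

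Section 8.1.2 (and the Summary) defines the primary outcome as yes or no for each patient. A patient improves by gaining at least one SAF-A point without worse fibrosis, or at least one fibrosis stage without worse steatohepatitis. Section 8.2 randomises 1:1 to LFMT or placebo capsules, with the synbiotic in both arms. Section 10 offers "analysis of a two-tailed one-sample t-test, or chi-square test" for the primary analysis.

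Section 11.3 says of the shared treatment: "Therefore, we expect a beneficial effect of the synbiotics in both study arms". It also describes the study in these terms: "this trial with adequate sample size endeavours to study if modification of the gut microbiome can attenuate NASH and liver fibrosis".

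**The concern.** The power statement is tied to the primary outcome, but it does not fit that outcome in three ways.

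- **Endpoint.** Section 4.4 sizes a reversal that includes steatosis and leaves out fibrosis. The 8.1.2 composite includes fibrosis and does not count steatosis.
- **Size.** For a binary endpoint compared between two arms of 24, a 25-point difference is hard to detect unless one arm is close to 0% or 100%.
- **Justification.** The GLP1 and synbiotic effects belong to treatment that both arms receive. Unless the synbiotic and LFMT interact, these effects raise the control rate and do not widen the difference between arms.

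A reader of 4.4 would take a null result as coming from a trial with an 80% chance of seeing the effect. If the chance is nearer one half, that result carries much less information. Section 11.3 also relies on adequacy of size when it weighs a burden that includes two liver biopsies.

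**Working it through.** **Inputs.** Alpha 0.05, power 0.80 and 24 per arm come from section 4.4, and 1:1 allocation from 8.2. The binary endpoint comes from 8.1.2. Section 8.5 replaces withdrawals, so 24 per arm is used without a dropout allowance. Two-sided testing is taken from section 10. The control rate is my assumption and is scanned, because the protocol gives none.

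**Can 24 be rebuilt?** Only in special cases that 4.4 does not state:

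- Unpooled normal formula, 0% vs 25%: n = (1.960 + 0.842)² × (0 + 0.25 × 0.75) / 0.25² = 7.85 × 3 = 23.5, so 24.
- Arcsine formula, 2% vs 27%: 24.0. One-sided pooled formula, 2% vs 27%: 24.
- One-sample test, 20% vs 45%: (1.960 × √0.16 + 0.842 × √0.2475)² / 0.25² = 23.1, so 24 in total, but this compares no arms.
- Two-sample t-test on a continuous score: 24 per arm detects a standardised difference of 0.826. A 25% reduction then needs an SD of about 0.25 / 0.826 = 0.30 of the mean.

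**Power for the composite, absolute 25 points.** I enumerated two binomials with n = 24 each and summed the probability of every table with p < 0.05. The control rate is p and the treated rate is p + 0.25.

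| Control rate | Chi-square (uncorrected) | Fisher |
|---|---|---|
| 0% | 0.89 | 0.75 |
| 2% | 0.79 | 0.66 |
| 5% | 0.69 | 0.56 |
| 10% | 0.58 | 0.46 |
| 20% | 0.47 | 0.36 |
| 30% | 0.45 | 0.33 |
| 40% | 0.45 | 0.33 |
| 50% | 0.45 | 0.34 |
| 60% | 0.51 | 0.40 |
| 70% | 0.69 | 0.56 |
| 75% | 0.89 | 0.75 |

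The pooled normal approximation gives 41–55% over control rates of 10–60%. One-sided testing gives 54–67% over the same range.

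**Relative reading.** A 25% relative increase in response gives exact chi-square power of 0.07 (20% vs 25%), 0.12 (40% vs 50%) and 0.16 (50% vs 62.5%). A 25% relative cut in non-response is a different scale; at 80% vs 60% it gives 0.33.

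**Size needed for 80%, absolute 25 points.** With p̄ the mean of the two rates, n = [1.960 √(2p̄(1−p̄)) + 0.842 √(p₁(1−p₁) + p₂(1−p₂))]² / 0.25². For 20% vs 45%, p̄ = 0.325 and n = (1.298 + 0.537)² / 0.0625 = 53.9, so 54. The other results are 36 at a 5% control rate, 43 at 10%, 61 at 30%, 62 at 35–40% and 58 at 50%.

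**Difference detectable at 80% with 24 per arm.** Solving the same enumeration for the difference, at control rates of 10, 20, 30, 40 and 50%:

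- Chi-square: 34.0, 37.7, 38.2, 37.9 and 36.2 points.
- Fisher: 38.2, 41.8, 42.2, 41.6 and 38.9 points.

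With the upper ends rounded up, that is about 34–39 and 38–43 points.

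**The case against.** The strongest reply is that no arithmetic error is proven. Section 4.4 leaves out so many inputs that the sponsor may have powered something else. A reduction in a parameter, with the pilot's necro-inflammation score behind it, could mean a continuous score, and an SD near 30% of the mean would then give 24 per arm. Section 10 speaks of baseline against endpoint with a one-sample test, and a one-sample calculation also lands near 24. This stands as far as it goes: a reader might infer that the sponsor miscalculated, and the document does not show that. But neither reading is stated in 4.4, and neither is a between-arm comparison of the composite that 8.1.2 makes primary.

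Two further limits also stand. First, a reader might infer that power is simply 45%, or that the trial has less than an even chance of success. Both depend on an assumed control rate and test. By chi-square, power is 0.58 at a 10% control rate, 0.51 at 60% and 0.69 at 5% or 70%. Second, the shared-treatment argument fails only if effects add. The Summary argues for combined approaches, so the sponsor may have an interaction in mind, but 4.4 does not claim one.

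A near-zero control rate is not a way out, because section 11.3 expects benefit from the synbiotic in both arms. The mirror case, with nearly every treated patient responding, does restore power, but the protocol nowhere assumes it.

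**Conclusion.** The point holds as a mismatch between the power claim and the endpoint, with missing inputs. It does not hold as a demonstrated slip in calculation. For the 8.1.2 composite compared between arms, with a 25-point difference and two-sided 5%, the stated 80% falls to about 45–58% by uncorrected chi-square or 33–46% by Fisher over control rates of 10–60%. Chi-square reaches about 80% only at control rates of about 0–2% or treated rates close to 100%. Fisher stays at or below 0.75 throughout. A relative 25% increase in response gives only 7–16% by chi-square for control rates of 20–50%.

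These figures rest on the assumed control rate, on the absolute scale (except for the relative figure) and on 24 evaluable patients per arm. The endpoint mismatch and the use of treatment effects common to both arms need no assumed rate; the latter needs only that no interaction is claimed.

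**What to change.** Keep 48 patients and amend the text.

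- **Section 4.4, inputs.** Name the 8.1.2 composite as the sizing endpoint. State the sponsor's own assumed control rate on synbiotic plus placebo with its source, whether the 25% is absolute or relative, and the test and sidedness.
- **Section 4.4, results.** Report the resulting power for 25 points, and the difference detectable at 80% with 24 per arm, as ranges over plausible control rates. For control rates of 10–50% the latter is about 34–39 points by chi-square or 38–43 by Fisher. No single control rate from this review should be written in as if it were the sponsor's.
- **Section 4.4, justification.** Remove the GLP1 and synbiotic benefits as support for the LFMT-versus-placebo difference, or state and justify an interaction.
- **Section 11.3.** Qualify the adequacy claim to match the restated power.

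The cost is a protocol amendment and a less favourable stated power. No patients or procedures are added. Holding to 80% for 25 points would instead take 36 to 62 per arm for control rates of 5–50%, which is not proposed here.

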## 5. TREATMENT OF SUBJECTS

### 5.1 Investigational product/treatment

#### *Allogenic Lyophilized Faecal Microbiota Transplantation (LFMT) capsules*

Fecal microbiota of vegan donors will be lyophilized, encapsulated in stomach acid resistant capsules (next generation enteric capsules; NGE capsules), and stored in -80°C (for an in depth description, see paragraph 6.8). Participants will ingest 21 capsules at the first 3 study visits (baseline, 8 weeks, 16 weeks), and will daily ingest 2 capsules. FMT of vegan donor contains a large amount of butyrogenic bacteria. FMT in itself is a safe therapeutic, and FMT administered via nasoduodenal tube showed no (serious) adverse events in our pilot study or other studies of this group (> 500 performed). Moreover, studies investigating LFMT capsules did not report an increase of any adverse events (see also paragraph 6.4). The LFMT capsules will be produced in the Amsterdam UMC, location AMC, under supervision of our pharmacist [name], who has experience in the research and production of LFMT capsules.

#### *A. soehngenii CH106*

*A. soehngenii* CH106 is a Gram-positive, catalase negative bacterium belonging to the clostridial cluster XIVa of the phylum Firmicutes and is a normal inhabitant of the human intestinal tract. *A. soehngenii* CH106 was produced at NIZO according to Hazard Analysis and Critical Control Points (HACCP) standards (see product dossier). After growth cells were harvested, washed and lyophilized in the presence of sucrose, maltodextrin, proline and NaCl. The freeze-dried powder was supplemented with maltodextrin, magnesium stearate and silicium oxide and capsulated in NGE caps to a final concentration of  $>1 \times 10^9$  cells per capsule.

#### *B. animalis subsp. lactis BLC1*

*B. animalis* subsp. *lactis* BLC1 is a Gram-positive, rod-shaped bacterium belonging to the Bifidobacterium genus of the phylum Actinobacteria and is commonly found in the human intestinal tract.

*B. animalis* subsp. *lactis* BLC1 was produced at SACCO Srl. in Italy according to Hazard Analysis and Critical Control Points (HACCP) standards and was obtained as a commercial product from SynBiotec (SynBiotec S.r.l., [name]).

### *Pasteurized A. muciniphila MucT*

Pasteurized *A. muciniphila* MucT (ATCC BAA-835T), abbreviated to pAkk, is a gram-negative anaerobic bacterium belonging to the phylum Verrucomicrobia. It is a 'commensal' bacterium, meaning that it is naturally found in the gastrointestinal tract of humans and animals in relatively significant quantities. In fact, it represents between 0.5 and 5% of all the bacteria colonizing the intestine. Its production in line with good manufacturing practice (GMP) and HACCP consists of an anaerobic fermentation followed by pasteurisation and concentration of the bacterial cells. The cells are then mixed with cryoprotectants and freeze-dried in order to produce a powder.

## **5.2 Use of co-intervention**

In addition to the FMT and probiotics, participants will receive FOS. This is discussed in the following chapters.

## **5.3 Escape medication**

Not applicable

## 6. INVESTIGATIONAL PRODUCT

### 6.1.1 Investigational product name and formulation

Allogenic Lyophilized Faecal Microbiota Transplantation (LFMT) capsules

### 6.1.2 Other product name(s) and formulation(s)

*Anaerobutyricum soehngenii* CH106

- Product name: *Anaerobutyricum soehngenii* CH106,  $\geq 1 \times 10^9$  live bacterial cells (per capsule).
- Product Sponsor: Caelus Health
- Product Manufacturer: NIZO
- Active compound: *Anaerobutyricum soehngenii* CH106
- Formulation: active compound and sucrose, dextrinized corn-starch, magnesium stearate, silica dioxide and NaCl
- One capsule to be ingested once daily before breakfast, with a glass of water
- If the participant misses a dose in the morning, they can continue to take the missed dose later in the day (before meal). Participants should resume the normal instruction on the following day and missed doses should not be moved to the following day.

*Bifidobacterium animalis* subsp. *Lactis* BLC1

- Product name: *Bifidobacterium animalis* subsp. *Lactis* BLC1,  $\geq 1 \times 10^{10}$  live bacterial cells (per capsule).
- Product Sponsor: Caelus Health
- Product Manufacturer: SACCO Srl
- Active compound: *Bifidobacterium animalis* subsp. *Lactis* BLC1
- Formulation: information will follow upon delivery (as it will be stated in the certificate of analysis)
- One capsule to be ingested once daily before breakfast, with a glass of water.
- If the participant misses a dose in the morning, they can continue to take the missed dose later in the day (before meal). Participants should resume the normal instruction on the following day and missed doses should not be moved to the following day.

*Pasteurized Akkermansia muciniphila* MucT

- Product name: pasteurized *Akkermansia muciniphila* MucT, around  $3 \times 10^{10}$  pasteurized bacterial cells (per capsule).
- Product Sponsor: A-Mansia Biotech
- Product Manufacturer: SACCO Srl
- Active compound: *pasteurized Akkermansia muciniphila* MucT
- Formulation: active compound and food excipients authorized for use in food for human consumption, being microcrystalline cellulose (E460), magnesium stearate (E470b), Talcum powder (E553b) and hydroxypropylmethylcellulose caps.
- One capsule to be ingested once daily 15 minutes before breakfast, with a glass of water.

- If the participant misses a dose in the morning, they can continue to take the missed dose later in the day (before meal). Participants should resume the normal instruction on the following day and missed doses should not be moved to the following day.

#### *Fructo-oligosaccharides*

- Product name: Frutalose® OFP
- Product Sponsor: Sensus BV provides the oligofructose as a gift to UMCA.
- Product Manufacturer: Sensus BV and co-packer (for tubs/ sachets)
- Active compound: oligofructose (fructo-oligosaccharides or oligo-saccharides)
- Formulation: Frutalose® OFP contains  $92 \pm 2\%$  oligofructose. Oligofructose is a polydisperse mixture of linear fructose polymers partly ended by a glucose molecule, coupled by means of  $\beta(2-1)$  bonds; it comprises a polydisperse mixture of linear fructose oligomers with degree of polymerization ranging between 2 and 10 units.
- Powder of 5 g to be ingested at same time daily after sprinkling on or mixed in foods (e.g. breakfast cereal/ porridge/ yoghurt) or drinks (e.g. coffee/ tea). Fresh orange juice is possible too provided immediately consumed after mixing. Soft drinks are not suitable due to very low pH. Powder will be delivered in sachets.
- If the participant misses a dose in the morning, they can continue to take the missed dose later in the day (before meal). Participants should resume the normal instruction on the following day and missed doses should not be moved to the following day.

## **6.2 Name and description of investigational product(s)**

Participants will be treated with either allogenic LFMT capsules of a vegan donor or capsules with saline placebo with brown pigment (NaCl 0.9%). Stool of lean vegan donors is collected, lyophilized (freeze-dried), encapsulated in NGE capsules, and stored in  $-80^{\circ}\text{C}$  (see paragraph 6.8). The day prior to the first study visit, participants will ingest laxatives (macrogol/kleanprep) to enhance engraftment. At the study visits at baseline, week 8 and 16, participants ingest 21 LFMT-capsules. All other days of the 24 week study period, participants ingest 2 LFMT capsules.

Daily, participants will have to take one capsule of *Anaerobutyricum soehngenii* CH106 ( $\geq 1 \times 10^9$  live bacterial cells), one capsule of *Bifidobacterium animalis* subsp. Lactis BLC1 ( $\geq 1 \times 10^{10}$  live bacterial cells), one capsule of pasteurized *Akkermansia muciniphila* MucT ( $\geq 3 \times 10^{10}$  pasteurized bacterial cells), and 5 grams of fructo-oligosaccharides.

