**Nature and extent of the burden and risks associated with participation, benefit and group relatedness:**

This study is a follow up to our previous intervention study aiming to examine the effect of FMT, now lyophilized and encapsulated, and in combination with synbiotic treatment and their underlying mechanisms of gut microbiota, in individuals with NASH.

*FMT-donors*

Fecal microbiotica will be collected of healthy, vegan donors. FMT-donors will be screened for infectious diseases through blood withdrawal and fecal analysis, which will be repeated after 1-2 months, and thereafter every 3 months.

*Recipient participants*

Individuals with NASH will be recruited from our outpatient clinic. After the screening is completed, participants will be telephoned with further instructions.

All individuals will have a total of four study visits, and time invested will approximately be 30 hours per person. At baseline and after 24 weeks, we will collect anthropometric data (e.g. body weight, height, waist circumference, bioelectrical impedance etc.). In addition, participants will hand in fecal samples at week 0, 2, 8, 10, 16, 18, and 24. Blood will be checked at week 0, 8, 16, and 24. Participants will, moreover, keep a diary of their daily food intake for 5 days in the week before and after study visits. In addition, they will fill in questionnaires physical endurance and quality of life at baseline and 24 weeks.

Participants will visit the study center at baseline (week 0), week 8, 16, and 24. On the first three visits, participants will ingest 21 LFMT capsules (or placebo) containing approximately

235mg of freeze-dried FMT (this equals 1500mg of fresh FMT) each. In addition, participants will ingest 2 LFMT-capsules (or placebo) daily for the duration of the study (24 weeks).

From the baseline visit until the end of the study (24 weeks later), patients will daily take 5 g FOS (powder). After baseline visit, participants will also ingest capsules of  $10^9$  *A. soehngenii* CH-106 cells,  $10^{10}$  *B. animalis* subsp. *lactis* BLC1 and  $3 \times 10^{10}$  pasteurized *A. muciniphila* cells. All of these will be taken in the morning. All bacterial strains and FOS are well researched on dosage, toxicity and adverse events, and show no serious hazards.

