#### 8.1.3 Secondary outcomes

##### Secondary outcomes

To demonstrate that the combined treatment improves:

- non-invasive outcomes of NAFLD, i.e. multiparametric MRI of liver and surrounding subcutaneous adipose tissue (MRI-PDFF, MR elastography, corrected T1), FibroScan Elastography and Controlled Attenuation Parameters, and plasma panel Enhanced Liver Fibrosis (ELF) panel, pro-C3.
- change in blood markers from baseline to end of treatment, namely: liver enzymes (i.e. alanine amino transferase (ALT), aspartate amino transferase (AST), gamma glutamyl transferase (GGT), alkaline phosphatase (ALP)), inflammatory blood markers (i.e. leukocytes, monocytes, CRP, IL-1( $\beta$ ), IL-6, IL-11, IL-17, IL-32, TNF- $\alpha$ , IFN- $\gamma$ , additional markers of inflammatory pathways), SCFA (i.e. propionate, butyrate, acetate), lactate, ethanol, plasma lipids (i.e. LDL, HDL, triglycerides, total cholesterol), FGF-21, adiponectin, leptin, lipopolysaccharides, zonulin, estrogen, vitamin B12, folate acid, other metabolomic and lipodomic outcomes.
- microbiome read outs (composition, engraftment, strain tracking) en metabolites, fecal SCFA-composition, and fecal albumine
- glycemic control, insulin resistance, body weight/BMI, waist circumference and percentage body fat
- MetSy criteria / %
- SCFA production and GLP1 gene and protein expression indicating GLP-1 production
- liver gene expression profile: lipogenic, inflammatory and fibrogenic pathways
- liver pathology, histopathological features, immunofluorescence and assessment of pathophysiological proteins

- NAFLD histology as assessed with a deep-learned algorithm scoring whole slide images of liver biopsies.
- 
- Continuous glucose monitoring (4x 7 consecutive days)
- quality of life (general (SF36) and NAFLD/NASH-specific (CDLQ-NAFLD)).

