#### *Physical examination*

At baseline and after 24 weeks, we will collect anthropometric data (e.g. body weight, height, waist circumference, bioelectrical impedance etc.).

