#### *Fecal samples*

In addition, feces will be collected at baseline, and after 2, 8, 10, 16, 18 and 24 weeks for extensive microbiota analysis and intestinal barrier function assessment.

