#### *Food diary, glucose monitoring and questionnaires*

Participants will, moreover, keep a diary of their daily food intake for 5 days in the week before and after study visits. In addition, they will fill in questionnaires physical endurance and quality of life at baseline and 24 weeks.

Last, continuous glucose measurements will be performed at house using portable devices, during a consecutive period of 1 week (7 days) in the week before baseline, week 1, 9, 17 and 25.

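### Nothing in the protocol places baseline stool, weight, waist and bioimpedance before the day −1 laxative, and the last of five listed glucose weeks (counted as four) falls after the 168-day treatment.

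*Protocol*

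**What the plan says.** **Laxative.** Section 6.2 is the only place that mentions it: "The day prior to the first study visit, participants will ingest laxatives (macrogol/kleanprep) to enhance engraftment". It applies to participants in both arms. Section 3 (study visits), Section 8.3 (procedures) and Section 11.3 (burden) do not mention it, and no laxative is stated before any later visit.

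**Stool.** Section 8.3 says "feces will be collected at baseline, and after 2, 8, 10, 16, 18 and 24 weeks for extensive microbiota analysis". The Summary's burden section says "participants will hand in fecal samples at week 0, 2, 8, 10, 16, 18, and 24". Section 3 puts blood and stool collection at the baseline visit, before the first capsules.

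**Anthropometry.** Section 8.3 says: "At baseline and after 24 weeks, we will collect anthropometric data (e.g. body weight, height, waist circumference, bioelectrical impedance etc". The corresponding secondary outcomes in Section 8.1.3 are "glycemic control, insulin resistance, body weight/BMI, waist circumference and percentage body fat".

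**Glucose.** Section 8.3 schedules 7-day recordings "in the week before baseline, week 1, 9, 17 and 25". The same list appears in Section 3 and twice in the Summary. The secondary outcomes in Section 8.1.3 read "Continuous glucose monitoring (4x 7 consecutive days", and the Summary's secondary outcomes and two places in Section 11.3 also say four.

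**Analysis.** Section 10 compares baseline with endpoint and plans paired tests: McNemar, paired t and Wilcoxon signed-rank.

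**The concern.** A laxative taken to help donor microbiota engraft is meant to change the gut contents that the baseline stool should describe. If that stool is passed after the laxative, the reference for composition, engraftment, strain tracking, fecal SCFA and fecal albumin is a purged sample, while the week-24 sample is not. Weight and impedance body fat are open to the same asymmetry through fluid loss. Recovery from the laxative would then be counted as change on treatment.

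This matters more here than in most two-arm trials. The objectives in Section 2 concern the synbiotic with and without LFMT, but all participants receive the synbiotic. No synbiotic-free arm exists, so its effect can be seen only as change from baseline.

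For glucose, a last recording made after dosing stops does not describe the end of treatment, and nothing in the protocol labels it as off-treatment.

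**Working it through.** **1. Order of events around baseline.**
- Day −1: laxative (6.2).
- Day 0: first visit, with stool collected or handed in and then the first capsules (Section 3; Summary). Anthropometry is at baseline (8.3).
- Week 24: Section 3 describes the same visit as baseline with a biopsy added. No laxative is stated.

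No section places the stool or the anthropometry before day −1.

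**2. What a distorted baseline does.** Let s be the effect of the synbiotic plus any change over time, f the added effect of LFMT, and d the shift from a purged baseline back to normal.
- Mean change, placebo arm: s + d
- Mean change, LFMT arm: s + f + d
- Difference between arms: (s + f + d) − (s + d) = f

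With the laxative given to both arms of a 1:1 randomised trial, d cancels on the additive scale in expectation. It does not cancel in either within-arm change, and those are what a paired test examines. The documents give no value for d, so neither its size nor a range can be computed.

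**3. Reach.** If stool is collected after the laxative, 1 of the 7 planned samples per participant is affected (weeks 0, 2, 8, 10, 16, 18, 24), in up to 24 + 24 = 48 participants. It is the sample against which the other 6 are compared.

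**4. Treatment length.** 24 × 7 = 168 days, which reproduces the 168 days given in Section 11.3.

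**5. Glucose weeks in study days.** Ordinal counting: week w runs from day 7(w − 1) to 7(w − 1) + 6. Elapsed counting: from day 7w to 7w + 6.

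| Week | Ordinal | Elapsed |
|---|---|---|
| 1 | 0–6 | 7–13 |
| 9 | 56–62 | 63–69 |
| 17 | 112–118 | 119–125 |
| 25 | 168–174 | 175–181 |

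Under either convention week 25 starts at or after day 168, and the last recording clearly on treatment is week 17. With the ±3-day margin, the final visit falls on days 165–171 (168 ± 3), or days 159–177 if three intervals each slip by 3 days (168 ± 9). Any overlap of week 25 with dosing would be incidental.

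**6. Count.** Pre-baseline, 1, 9, 17 and 25 make 5 recordings, against 4 stated.

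**7. Side effect.** If the pre-baseline glucose week runs up to the visit (days −7 to −1), 1 of its 7 days is the laxative day.

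**The case against.** **The order is inferred.** The protocol never says that the stool is passed after the laxative. Samples are handed in, which fits a home sample passed earlier, and the figure giving the visit overview is not shown in the text available. Section 3's account of the baseline visit does not list weight or impedance, and Section 8.3 says only that they are taken at baseline. This stands: a purged baseline is the plain reading, not an express statement. But nothing in the text directs staff to collect before the laxative, and Section 8.3 does not tell them that a laxative is given.

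**The randomised comparison is safe.** This also stands. A reader might infer that the trial's main comparison is biased; it is not, because both arms take the laxative. Nor can one argue that a purged baseline is a noisier covariate, since Section 10 names no covariate-adjusted model. Within-arm change is uncontrolled even with a clean baseline, but the laxative adds an avoidable component to it.

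**Body composition is wider than weight and impedance.** Correct. Visceral and subcutaneous fat are measured by MRI before baseline, so those outcomes are unaffected.

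**Week 25 follows a pattern.** Weeks 1, 9, 17 and 25 each follow a visit, and the protocol says that donor FMT affects the recipient's microbiota for 8–12 weeks, so week 25 is not a washout of FMT. That is fair, but the argument covers FMT and not the daily synbiotic. Weeks 1, 9 and 17 follow a loading dose; no loading dose is scheduled at week 24. Weeks 1, 9 and 17 remain usable as on-treatment recordings.

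**Conclusion.** The point holds in a limited form. As written, the schedule plausibly gives a post-laxative baseline for stool, weight, waist and bioimpedance, and it lists no glucose recording after week 17 that is nominally on treatment. The consequence is confined to within-participant change in secondary, mechanistic outcomes: microbiome composition, engraftment, strain tracking, fecal SCFA and albumin, weight and impedance body fat, and the glucose endpoint.

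The documents do not support the claim that all 48 baseline samples are known to be purged, that the arm comparison is biased, or that MRI fat or the histological primary endpoint is affected. The size of the laxative effect is unknown.

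The conclusion assumes that baseline means the first visit and that dosing ends at the nominal 168 days. The disagreement between five and four glucose recordings needs no assumption; it is a plain contradiction. A change is worth making now, because a pre-laxative baseline cannot be recovered once dosing has begun.

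**What to change.** These changes concern measurement timing and wording only.

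1. In Section 8.3, state that baseline stool, weight, waist and bioimpedance are obtained before the laxative, for example with a home stool kit and with body measurements taken at screening. Mention the laxative in Sections 3 and 8.3 so that the order is visible to staff.
2. Schedule the final glucose week in the 7 days before the week-24 visit (days 161–167). Otherwise label week 25 as an off-treatment recording and do not use it as the on-treatment endpoint.
3. State whether the pre-baseline glucose week includes the laxative day.
4. Give one number of glucose recordings in the Summary (intervention, secondary outcomes, burden) and in Sections 3, 8.1.3, 8.3 and 11.3.

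The cost is schedule text and a stool kit handed out at screening. The downside is small: the baseline stool is a few days older. Measurements taken at screening may be older than that, since the interval from screening to baseline is not stated.
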